#### 1.11.3.3 Allocation to Interventions

After the baseline visit, the subjects will be randomized to either of the two treatment arms (1:1 randomization) according to permuted blocks of varying length. Randomization will be stratified by site in order to prevent unbalanced allocation of the intervention of interest and the control intervention to sites. It will be implemented as a central 24-7 Internet service operated by local, authorized study staff. Treatment assignments will be displayed on screen and delivered by e-mail. The randomization service will be maintained by the IMSB, University of Cologne.

#### 1.11.3.4 Post-treatment phase

End-of-treatment primary and secondary outcomes (T2) will be gained in week 10 after completion of all 15 therapy sessions. The following outcomes will be obtained by the blinded rater at the end of treatment:

a) *Questionnaires:*

- Geriatric Depression Scale (GDS)
- Quick Inventory of Depressive Symptomatology Clinician-Rated Version (QIDS-C)
- Geriatric Anxiety Inventory (GAI)
- Patient-Reported Outcome in Major Depressive Disorder (PRO-MDD)
- WHO Quality of Life (WHOQOL-OLD and WHOQOL-BREF)
- Health Status (SF 36)
- Insomnia Severity Index (ISI)
- Epworth Sleepiness Scale (ESS)
- REM Sleep Behavior Disorder Screening Questionnaire (RBDSQ)

A qualitative interview will be performed at the end of the treatment period to assess individuals' needs and goals met and not met by the intervention.

If applicable to subject:

b) *Blood measurement:*

After completion of the treatment (T2) venous blood samples will be obtained from the subject for epigenetic analyses, measurement of Amyloid- $\beta$ , NFL, PBMCs, Metabolomics, Proteomics and miRNA analyses. The total volume of the blood draws will not exceed 50 ml.

c) *MRI:*

A Magnetic Resonance Imaging (MRI) acquisition of the subjects' brain will be performed at T2 to obtain a high-resolution structural image (T1 and T2 FLAIR) of the subjects' brain after the psychotherapeutic intervention. Furthermore, a resting-state fMRI will be acquired as well as Diffusion Tensor Imaging (DTI) of the subjects' brain at end-of-treatment (T2).

#### 1.11.3.5 Final examination

6 months after randomization the final follow-up visit (T3) will be performed. Following primary and secondary outcomes will be obtained at the follow-up visit:

a) *Questionnaires:*

- Geriatric Depression Scale (GDS)
- Quick Inventory of Depressive Symptomatology Clinician-Rated Version (QIDS-C)

- Geriatric Anxiety Inventory (GAI)
- Patient-Reported Outcome in Major Depressive Disorder (PRO-MDD)
- WHO Quality of Life (WHOQOL-OLD and WHOQOL-BREF)
- Health Status (SF 36)
- Insomnia Severity Index (ISI)
- Epworth Sleepiness Scale (ESS)
- REM Sleep Behavior Disorder Screening Questionnaire (RBDSQ)
- Consortium to Establish a Registry for Alzheimer's Disease neuropsychological battery (CERADplus)
- Subtests of the Neuropsychological Assessment Battery (NAB) Screening Module (Executive Functions: Maze)
- Longitudinal Interval Follow-up Evaluation (LIFE)

Furthermore, the history of cognition (subjective cognitive decline) will be assessed at the follow-up visit. A qualitative interview will be performed at the follow-up visit to obtain the medical history during the period from end-of-treatment (T2) to the follow-up visit (T3). This assessment includes but is not limited to the medication history, psychological/psychotherapeutic interventions, other psychiatric interventions (e.g. ECT, TMS, tDCS) and psychosocial stressors in the time interval from end-of-treatment (T2) to follow-up (T3).

If applicable to subject:

b) *Blood measurement:*

At the follow-up visit venous blood samples will be obtained from the subject for epigenetic analyses, measurement of Amyloid- $\beta$ , NFL, PBMCs, Metabolomics, Proteomics and miRNA analyses. The total volume of the blood draws will not exceed 50 ml.

c) *MRI:*

A Magnetic Resonance Imaging (MRI) acquisition of the subjects' brain will be performed during the follow-up visit to obtain a high-resolution structural image (T1 and T2 FLAIR) of the subjects' brain. Furthermore, a resting-state fMRI will be acquired as well as Diffusion Tensor Imaging (DTI) of the subjects' brain at follow-up (T3).

#### 1.11.3.6 Examination hierarchy and time windows

The screening and the baseline outcome assessment T0 can be performed in one combined visit. In case of separation of screening and baseline assessment, they have to be administered within the same week. This may be necessary for relief of the subjects.

The first treatment session has to be completed within one week after the screening visit. The 15 successive treatment sessions in both groups (LLD-CBT and LLD-SUI) have to be performed in a bi-weekly manner of 50-minute individual face-to-face treatment sessions. If a treatment session can not be proceeded (e.g. sickness of a subject or therapist) it has to be rectified and the session has to be completed within the following week.

The T1 outcome assessment will be performed by the rater in week 5. The outcome assessment T2 at the end of treatment will be carried out in week 10. The follow-up assessment T3 will be performed 6 months after the initial randomization of the subject.

#### 1.11.4 Trial conditions and restrictions

##### 1.11.4.1 Medical surveillance

The enrollment into the trial at the screening visit will be performed by the study psychologist or physician. The study physician will perform the venous blood draw from a peripheral vein and be present during the MRI, if applicable. At all trial sites a trial physician and other medically trained employees will be present at the unit.

During all phases of the trial, i.e. from screening until final examination, the subjects can contact medically trained employees at the trial centers and by [contact] Precaution and emergencies

It should be stressed that this study does not include risk or harm for the subject. CBT and the control intervention are supportive and goal directed, which limits the risk to a minimum. Neither the intervention of interest nor the control intervention is associated with a significant risk for the subjects. In contrast, it is most likely that both interventions will be of benefit for the subjects (the superiority of LLD-CBT with regard to this benefit is being tested in this trial). None will confront the subjects with negative contents, such a reactivation of trauma as an example. In contrary, both interventions are supportive and aim at stabilizing the mental status of the subjects. The assessments of outcome are also not associated with risk. The Investigators will ensure that the trial is conducted in complete conformance with the principles of Good Clinical Practice (GCP) and the Declaration of Helsinki. Still, adverse events and serious adverse events will be recorded at every visit and will be reported to a data safety and monitoring board (DSMB) on a continuous basis. For any signs or symptoms or adverse events, a causal or symptomatic treatment according to standard medical practice will be performed, if deemed necessary by the Investigator.

#### 1.11.4.3 General restrictions

During the study, including the follow-up visit, subjects are not allowed to participate in any other clinical trial. They are also not allowed to gain additional inpatient or outpatient psychological/psychotherapeutic treatment throughout the treatment period. Furthermore, subjects must be free of antidepressive medication or have a stable antidepressive pharmacological treatment during the 8-week intervention. The scheduled, regular use of Benzodiazepines (not PRN) is not allowed during the study.

### 1.12 TRIAL VARIABLES

#### 1.12.1 Demography

The demographic data to be collected for this trial include i.a.: sex, age, marital and family status, family history, housing situation, education, occupation, nationality/ethnicity, psychiatric and psychotherapeutic history and present treatment, medication, somatic symptoms and diseases, weight, height, BMI, level of physical activity.

#### 1.12.2 Adverse events

##### 1.12.2.1 Definition of adverse events

An adverse event (AE) is any untoward medical occurrence in a patient or clinical investigation subject which does not necessarily have a causal relationship with this treatment. An AE can therefore be any unfavorable and unintended sign, symptom, or disease temporally associated with the treatment, whether or not considered related to the treatment.

In this study adverse events are defined and assessed as:

1. Worsening of symptoms e.g. generalisation of symptoms,
2. Occurrence of new symptoms,
3. Occurrence of passive suicidal thoughts,
4. Occurrence of active suicidal intentions or plans,
5. Occurrence of problems in the patient-therapist relationship,
6. Private problems,
7. Occupational problems,
8. Further adverse events (e.g. Influenza, fractures etc.).

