### 1.7.1 Benefit/risk analysis

The study is not expected to harm any patient or include significant risk for the patient. The individual taking part in this trial will either receive the full LLD-CBT program or the SUI control intervention, which will both provide

benefit and represent substantially more treatment than regular health care. The study is a highly beneficial offer for LLD patients because it provides treatment in both arms, which is usually not provided to these patients in standard care. The risk for the participating individual during the diagnostic procedures or outcome assessments is minimal. The intervention is of limited length and is expected to improve outcome. None of the interventions will confront the patients with negative contents, such as reactivation of trauma as an example. In contrary, both interventions are supportive and aim at stabilizing the mental status of the patients. The interventions will be provided by experienced psychotherapists, which will also limit the risk of harm. The Investigators will ensure that the trial is conducted in complete conformance with the principles of Good Clinical Practice (GCP) and the Declaration of Helsinki. Still, adverse events and serious adverse events will be recorded at every visit and will be reported to a data safety and monitoring board (DSMB) on a continuous basis. Although side effects of evidence-based psychotherapies such as CBT are very rare, possible undesired effects may include a transient worsening of symptoms or risk of suicidality. For any signs or symptoms or adverse events, a causal or symptomatic treatment according to standard medical practice is performed, if deemed necessary by the Investigator.

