| a)                                                      | Concomitant medication | Recording of any concomitant medication after signature of informed consent at baseline.                                                                                                                                                                                                                                                                                                                                                                                                                                                                                                                         |
| b)                                                      | SAEs, AEs              | Recording of any spontaneously reported or observed SAEs and AEs after signature of informed consent until end of trial.                                                                                                                                                                                                                                                                                                                                                                                                                                                                                         |
| Voluntary procedures (after separate consent is given): |                        |                                                                                                                                                                                                                                                                                                                                                                                                                                                                                                                                                                                                                  |

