### 1.11.3 Course of the trial

The first visit of the study will be a screening/enrollment and baseline (T0) visit. The screening and baseline assessment can either be performed in a combined visit or in two separated visits (screening and baseline) within the same week for relief of the subjects.

Prior to screening the subjects will be informed about the study and the informed consent will be obtained. The inclusion and exclusion criteria as well as the primary outcome will be assessed. Only in those subjects who pass the screening procedure the secondary outcomes (baseline, T0) will be obtained.

The enrollment into the trial prior to screening will be performed by the study psychologist or physician. The study physician will obtain separate consent for participation in blood & MRI testing, if applicable. The outcomes will be obtained by the rater, who will be blinded to the later treatment arm allocation.

After the baseline assessment (T0), the subjects will be randomized to either of the two treatment arms (1:1 randomization). Within one week, the first of the successive bi-weekly 50-minute individual face-to-face treatment sessions will be performed by a study therapist.

After 7 therapy sessions, the primary and secondary outcomes will be obtained in week 5 (T1) by the blinded rater. This will be followed by the treatment sessions 8 to 15 which will be carried out by the therapist. End-of-treatment primary and secondary outcomes will be obtained in week 10 (T2) after completion of all 15 therapy sessions. The final follow-up assessment (T3) will be performed 6 months after randomization at the follow-up visit by the blinded rater.

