#### 1.12.2.8 Adverse event recording and reporting

The risk of CBT and of the control intervention is minimal. Theoretically psychotherapeutic intervention can be harmful by inducing worsening of symptoms. CBT and the control intervention, however, are supportive and goal directed, which limits the risk to a minimum. The interventions will be provided by experienced psychotherapist, which will also limit the risk of harm. Still, adverse events and serious adverse events will be recorded at every visit and captured in the eCRF. A data safety and monitoring board (DSMB) will be established, to which safety data will be reported on a continuous basis.

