##### 2.6.4.1.1 Adverse events

Adverse events are listed and summarized by group and category, seriousness, severity, relatedness, respectively.

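### Symptom worsening, one of two harms the protocol names, has no operational definition as an adverse event, and the SAP counts no worsened patients from the GDS and QIDS-C data already collected

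*Combined protocol and SAP*

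**What the plan says.** Protocol 1.7.1 states that "possible undesired effects may include a transient worsening of symptoms or risk of suicidality", and 1.12.2.8 repeats the first of these: "Theoretically psychotherapeutic intervention can be harmful by inducing worsening of symptoms". Suicidality has its own assessment at every visit, with a three-level risk table (1.12.2.7, Table 4).

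Worsening is the first of eight AE categories in 1.12.2.1: "Worsening of symptoms e.g. generalisation of symptoms". No scale, amount or comparison time is attached. Intensity is graded on the generic scale of Table 3, by limitation of usual activities.

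On capture, footnote b to Table 2 reads "Recording of any spontaneously reported or observed SAEs and AEs after signature of informed consent until end of trial", and 1.12.2.8 says "adverse events and serious adverse events will be recorded at every visit and captured in the eCRF". On staff, 1.11.3 says "the first of the successive bi-weekly 50-minute individual face-to-face treatment sessions will be performed by a study therapist", and 1.11.3.3.2 has the same therapist deliver both interventions. The Investigator judges causality (1.12.2.4) and, for suicidality, also intensity and risk level (1.12.2.7). No section says who asks about or records worsening, or whether that person is masked.

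GDS and QIDS-C are scheduled at screening/baseline, T1, T2 and T3 (Table 2), with a blinded rater (1.9.3). SAP 2.6.3 and 2.6.4 analyse change by MMRM, mixed models or GEEs. For AEs, SAP 2.6.4.1.1 says "Adverse events are listed and summarized by group and category, seriousness, severity, relatedness, respectively".

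**The concern.** The trial will publish a by-arm count of worsening as an adverse event. Two assessors could apply category 1 differently to the same patient, because nothing says how much worse, on what, or compared with when. Most occasions for noticing worsening arise in sessions where the arm is known, and no stated step keeps the assessment independent of that knowledge. A difference between arms in this row, or its absence, would therefore be hard to interpret.

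The efficacy analysis does not fill the gap. A mean difference in GDS change can favour one arm without showing how many patients in either arm ended above their starting score. The scores that would show it are already in the database, collected on the same schedule in both arms, and one of the two scales is rated by a masked clinician.

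**Working it through.** **1. Visits with AE evaluation (Table 2).** Visits 2 to 19 give 18 visits. Therapy sessions are visits 2 to 8 (7) and 10 to 17 (8), so 7 + 8 = 15, and 15/18 = 83%. The other three (9, 18, 19) are T1, T2 and T3, with the blinded rater.

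**2. Scale-based counts of worsened patients planned.** None in protocol 1.14.3 or SAP 2.6.3 to 2.6.4.2. GDS and QIDS-C each have three post-baseline assessments.

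**3. The plan's own figures (protocol 1.14.1, SAP 2.1.7).** Mean pilot GDS change: CBT 10.67 − 19.26 = −8.59; SUI 14.92 − 20.68 = −5.76. The difference of 2.83 matches the plan. The 99 per group for d = 0.4 reproduces, and 99/0.8 = 123.75, rounded up to 124. None of these is disputed here.

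**4. Illustration of how often a measured rise might occur.**
- SD of change = √(SDpre² + SDpost² − 2r·SDpre·SDpost), with the plan's r = 0.5.
- CBT: √(3.92² + 6.42² − 3.92 × 6.42) = √31.42 = 5.61.
- SUI: √(3.96² + 7.58² − 3.96 × 7.58) = √43.12 = 6.57.
- Under normality, with a half-point continuity correction, P(rise ≥ k) = 1 − Φ((k − 0.5 − mean change)/SD).
- For k = 3: CBT 1 − Φ(11.09/5.61) = 2.4%; SUI 1 − Φ(8.26/6.57) = 10.4%.

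The plan gives no individual threshold, so three are shown. The range of r from 0.3 to 0.7 is an assumption.

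| GDS rise | CBT, r = 0.5 (range) | SUI, r = 0.5 (range) | Expected of 99 per arm, r = 0.5 |
|---|---|---|---|
| ≥ 1 | 5.2% (2.5–7.9) | 17.0% (13.1–20.0) | 5 vs 17 |
| ≥ 3 | 2.4% (0.8–4.3) | 10.4% (6.9–13.3) | 2 vs 10 |
| ≥ 5 | 1.0% (0.2–2.1) | 5.9% (3.3–8.4) | 1 vs 6 |

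**5. Precision.** For 2.4% vs 10.4% with 99 per arm, SE = √(0.024 × 0.976/99 + 0.104 × 0.896/99) = 0.034. The 95% half-width is 1.96 × 0.034 = 6.7 percentage points around a difference of 8.0. Two-sided power at 99 per arm, over thresholds of 1 to 5 points and this range of r, is about 37% to 80%. With no events in 99 patients, the exact 97.5% upper bound is 3.7%.

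**6. Missing scores.** At the planned 20% attrition, 124 − 99 = 25 per arm may lack a score, or 25/124 = 20%. That exceeds every CBT rate in the table and equals the highest SUI rate, so the handling of these patients must be visible.

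**Limits.** The pilot values describe one follow-up time, which the plan labels 6 months post randomization, so they need not apply at T1 or T2 and do not give the chance of worsening at any of three visits. The normal model ignores the 0–30 bounds. The rates indicate how common a measured rise might be; they say nothing about bias in AE recording.

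**The case against.** Several stronger readings are tempting, and the documents do not support them.

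- **Worsening is captured only if patients volunteer it.** Footnote b also covers observed events, 1.12.2.1 lists worsening among the categories to be assessed, and recording is required at every visit. Worsening can also surface as a reason for stopping (1.10.4.3), as hospitalization (1.12.2.2) and in LIFE at T3. What stands: no structured question is given, stopping and hospitalization catch only severe cases, and no worsening count is planned from LIFE.
- **The AE comparison merely reflects how unmasked therapists report.** No section says therapists record AEs, and the Investigator's judgement is required. Therapists' expectations are measured (1.9.2), the same therapists deliver both arms, sessions are filmed, and a DSMB receives safety data continuously. What stands: the assessor and their masking are unspecified.
- **The trial will formally conclude whether CBT harms patients relative to SUI.** The plan sets no comparative safety objective and no test, only listings and summaries by group. What stands: by-arm summaries invite comparison, so the row should mean something definite.
- **The scales should replace category 1.** The protocol speaks of transient worsening. Three assessments can miss episodes that every-visit recording would catch, so both are needed.
- **Category 5, "Occurrence of problems in the patient-therapist relationship", is under-reported and needs its own instrument.** Reluctance to report is plausible but undocumented, and does not justify a new form.

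SAP 2.6.4 also summarises quantitative outcomes by percentiles, including the extremes. That shows spread but does not count patients above their own baseline.

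**Conclusion.** The point holds as a gap in definition and analysis. It does not demonstrate bias. A named harm has no operational definition as an AE, its assessor and their masking are not stated, and uniformly collected data that could describe it are not used for that purpose. The visit count and the absence of a planned deterioration analysis rest on the text alone.

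The 2.4% vs 10.4% illustration rests on the pilot means and SDs, r = 0.5, normality and a 3-point cut-off chosen only to show scale. It suggests that a table would not be empty, and that it would be descriptive. A reader might take the plan's 2.5 GDS points as a ready-made threshold for worsening; it is a difference between group means and says nothing about when an individual has deteriorated. A reader might also treat GDS as a masked measure. It is self-rated by patients who are not described as masked, so it is uniform across arms but unmasked; QIDS-C is the masked one. The primary efficacy test is unaffected.

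**What to change.** In SAP 2.6.4.1, add a descriptive table alongside AE category 1, and keep category 1 as it is:

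1. Number and percent of patients by arm scoring above their own baseline at T1, T2 and T3, for QIDS-C (masked) and GDS (uniform, self-rated, unmasked).
2. Two levels for each scale: any rise, and one larger rise that the sponsor prespecifies and justifies as an individual-level threshold.
3. Risk difference with 95% CI at each visit.
4. Patients with missing scores, and patients stopped for worsening under 1.10.4.3, shown separately, plus a sensitivity row counting them as worsened. This row is a bound, because follow-up after stopping is only attempted where feasible (1.10.4.2).

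State also who assesses AEs at therapy visits and whether that person knows the arm.

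The cost is one SAP paragraph and one table from data already collected, with no added patient burden. Because 1.14.3 requires the SAP to be final before enrollment, a later addition should be a dated addendum written before the randomization code is released. The downsides are a little more analysis work, limited precision, and that episodes between assessments remain visible only in the AE record.
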